### Sample size

The sample size of the trial is estimated using PASS 15 Power Analysis and Sample Size software (NCSS, Kaysville, UT, United States). Assuming that the standard deviation (SD) is 32.9 mmol·min/L, a sample size of *n* = 39 provides 90% power to detect a change of 20 mmol·min/L in iAUC (*p* < 0.05) with Bonferroni correction, based on the previous study (36). Anticipating a 20% dropout rate, 49 subjects should be enrolled to obtain a final sample size of 39. Considering participants enrolled in four hospitals, 52 subjects will be enrolled with 13 subjects for each center.

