### Statistical analysis

The incremental areas under the curve (iAUC) will be calculated by using the trapezoidal rule (37) for PGR. All areas below pre-prandial glucose are excluded from the calculations. Two-factor repeated-measures analysis of variance (ANOVA) is performed to analyze the effects of treatment × time on outcome variables measured over the crossover study period, including iAUC for PGR and post-prandial glucose excursion. When treatment and time interaction are statistically significant, one-factor ANOVA and Bonferroni's *post-hoc* tests for multiple comparisons are performed to investigate the effect of treatment on the aforementioned measurement of PGR. Comparison between baseline and end-points is assessed by paired Student's *t*-test. Values are presented as mean ± SEM unless otherwise indicated. *P*-values of <0.05 are considered statistically significant. All analyses are performed with SPSS software version 25 (SPSS Inc., Chicago, IL, USA).

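### Bonferroni post-hoc tests for the meal contrasts are valid, but Holm's step-down version would keep the same 5% family-wise error and regain some power at almost no cost

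*Protocol article*

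**What the plan says.** The Statistical analysis section of the protocol article plans a two-factor repeated-measures ANOVA first. The meal contrasts follow conditionally: "When treatment and time interaction are statistically significant", then "one-factor ANOVA and Bonferroni's *post-hoc* tests for multiple comparisons are performed". The significance level is 0.05; whether tests are one- or two-sided is not stated.

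The Sample size section uses the same correction. It begins "Assuming that the standard deviation (SD) is 32.9 mmol·min/L" and continues that "a sample size of *n* = 39 provides 90% power" "to detect a change of 20 mmol·min/L in iAUC", again with Bonferroni. The number of comparisons is not given there.

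The Primary outcome section compares the pre-load (P + L) and snack (S + L) meals with co-ingestion (CL) and water (W + L). Read literally, that is four contrasts; testing every pair of the four meals would make six. No step-down procedure is mentioned and no reason is given for single-step tests.

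**The concern.** Under Bonferroni, each of m contrasts is tested at 0.05/m whatever the others show. Holm tests the smallest p-value at 0.05/m, the next at 0.05/(m − 1), and so on, stopping at the first failure. It needs no further assumption, so the shared controls and the within-woman correlation in this crossover raise no difficulty.

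The choice matters most when several contrasts are real together. That is plausible here, because each biscuit strategy is compared with two controls and the rationale expects benefit. With 39 evaluable women, a real difference from one control could be reported as not significant under Bonferroni when Holm would have declared it significant at the same family-wise error rate.

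**Working it through.** **Inputs.** From the Sample size section: n = 39, effect 20 mmol·min/L, SD 32.9 mmol·min/L, power 90%. From Primary outcome: m = 4 on the literal reading, with m = 6 (all pairs) as the alternative. Assumed: 32.9 is the SD of the within-woman difference; tests are two-sided; errors are normal with equal variances and correlations.

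**Step 1: reproduce the plan's figure.** For a paired comparison with the normal formula,

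n = [SD × (z(1 − 0.05/(2m)) + z(0.90)) / effect]².

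With m = 4: [32.9 × (2.498 + 1.282) / 20]² ≈ 38.7, rounded up to 39. This matches the stated n and makes the paired reading of 32.9 plausible, though it does not prove it. Dropout: 39/0.8 = 48.75, so 49, as stated.

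**Step 2: single-contrast power with the t distribution.** The standardised effect is 20/32.9 = 0.608. At n = 39 the noncentral t gives 87.3% power at 0.05/4 = 0.0125 and 83.7% at 0.05/6 = 0.0083.

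**Step 3: the thresholds.** For m = 4, Bonferroni uses 0.0125 four times; Holm uses 0.0125, 0.0167, 0.025 and 0.05 in order of p-value. The first step is identical, so power for at least one rejection is identical too.

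**Step 4: simulation.** 40,000 trials per scenario, 39 women, four meals each, error SD per meal 32.9/√2 = 23.3 so that each paired difference has SD 32.9. Both methods were applied to the same paired t-test p-values. The treatment × time gate was not modelled. Each entry is Bonferroni → Holm.

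| Family | Real contrasts, each of size 20 | Average power per real contrast | All real contrasts significant | At least one rejection |
|---|---|---|---|---|
| 4 | all four | 87.2% → 93.9% | 65.9% → 85.5% | 99.3% both |
| 4 | two (one strategy against both controls) | 87.2% → 89.0% | 79.0% → 82.5% | 95.7% both |
| 6 | four (both strategies against both controls) | 83.6% → 88.2% | 58.5% → 70.8% | 98.9% both |
| 6 | three (one meal differs from the other three) | 83.7% → 86.3% | 66.5% → 72.8% | 96.7% both |

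**Step 5: error control.** With no real difference, the family-wise error was the same for both methods: 4.5% (m = 4) and 4.2% (m = 6). With two of four contrasts real, it was 2.3% for Bonferroni and 4.2% for Holm. The extra power comes from error allowance that Bonferroni leaves unused; the 5% limit holds. In every simulated trial Holm rejected everything that Bonferroni rejected.

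**The case against.** The strongest reply is that nothing here is wrong. Bonferroni is valid, it is pre-specified, and the Sample size and Statistical analysis sections agree on it. That stands. A reader might infer that the correction is an error or that it undermines n = 39; the documents support neither, since n = 39 reproduces with Bonferroni at m = 4.

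A reader might also take the rise from 66% to 86% for all four contrasts as the size of the problem. The protocol does not support that. It sets 90% power for a change of 20 and nowhere requires all four contrasts to succeed. That scenario also forces CL and W + L to have the same mean response, although Table 2 gives them 46.2 g and 38.1 g of carbohydrate. With two of four contrasts real, the average gain is only about 2 points.

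Two further limits stand. The protocol does not say what 32.9 is the SD of. And the simulated tests are ungated paired t-tests, so the power levels are not those of the analysis as written. Holm's advantage in direction does not depend on this: once the contrasts are reached, it never rejects less on the same p-values.

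Finally, Bonferroni tests agree with Bonferroni simultaneous intervals. A Bonferroni interval excludes zero exactly when the Bonferroni test rejects, so every additional Holm rejection would sit beside an interval that includes zero. That is a genuine reason someone might prefer single-step tests. It can be handled by wording, but it should be stated openly.

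**Conclusion.** The point holds as an optional efficiency improvement. For deciding which meals differ, Holm on the same family is never worse than the planned tests and is better whenever at least one contrast is rejected and another falls between the two thresholds.

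Under the assumptions listed in the working, the gain in average power per real contrast is about 2 to 7 points for a family of four, depending on whether two or all four contrasts are real, and about 3 to 5 points for all six pairs. The exact size depends on the family and on the number of real effects, neither of which the protocol fixes. The direction holds for any family of two or more contrasts.

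**What to change.** In the Statistical analysis section, replace the Bonferroni post-hoc tests with Holm-adjusted p-values on the same family of within-woman meal contrasts, specified before the data are analysed. The sample-size sentence can stay on Bonferroni as a conservative basis.

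Add one sentence on intervals. If Bonferroni simultaneous 95% intervals are kept, say that significance is decided by the Holm p-value and that the intervals are conservative and may include zero for a contrast declared significant. Alternatively, report unadjusted 95% intervals and label them as such.

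The cost is one or two sentences. Holm p-values follow from sorting the unadjusted ones, so design, sample size and data collection are untouched. The remaining price is the possible visible mismatch between a significant p-value and its interval. The interaction gate is a separate matter that this change leaves as it is.

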A dietary strategy confirmed to be effective for reducing PGR individually is of paramount importance in increasing compliance with a recommended meal plan. Therefore, to optimize the use of low-GI biscuits in reducing individual PGR and provide valuable information in clinical practice of preventing T2DM for post-partum women with recent GDM, this proposed study will be conducted in two phases. The first phase (week 1) is designed with a randomized crossover trial with the main objective to compare the effect of low-GI biscuits consumed as pre-loads or as mid-meal snacks on individual PGR of the following main meal assessed by CGM. In the second phase (weeks 2–5), individualized intervention either with pre-loads or mid-meal snacks will be conducted depending on the results of personal PGR from the first phase. The objectives of the second phase are to observe before–after differences among all participants in their glycemic control using CGM metrics and glycated albumin (GA), dietary behavior, and psychosocial factors and compare those differences between the two dietary strategies. This article presents the development of the study design and procedure.

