**Figure 1 F1:**
[figure not shown]
Randomized crossover design. Participants will complete four test meals over 4 consecutive days in a randomized counterbalanced order using Latin Square Design. Participants will be randomized to receive one of the four meal arrangement orders as follows: (1) P + L → S + L → W + L → CL; (2) S + L → CL → P + L → W + L; (3) CL → W + L → S + L → P + L; (4) W + L → P + L → CL → S + L. To diminish the glycemic impact from the last meal, breakfast, lunch, pre-load, and mid-meal snack foods are provided, with breakfast and lunch identical for 4 test days. 3h-iAUC after each lunch using continuous glucose monitoring (CGM) will be calculated as the primary outcome (P, Pre-load; S, Mid-meal snack; B, Breakfast; L, Lunch; W, Water; C, Co-ingestion; iAUC, Incremental areas under the curve of post-prandial glycemic response; P + L, Fitmeal pre-load 30 min before lunch; S + L, Fitmeal as mid-meal snack 2 h before lunch; CL, Co-ingestion of Fitmeal with lunch; W + L, Drinking water 30 min before lunch).

Moreover, a before–after intervention of 4-week duration based on within-subject meal test results will be followed for all participants to compare changes in PGRs from the baseline. The study will be carried out at four maternal and child healthcare hospitals in Chengdu. The protocol (CWCCH 2021027) has been approved by the ethics committee of Chengdu Women's and Children's Central Hospital, and written informed consent has been obtained from all participants. The study is conducted in accordance with the principles expressed in the Declaration of Helsinki.

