After removing CGM, each participant will receive a 20-min face-to-face counseling from a trained healthcare provider in each research site, including the explanation of baseline CGM glucose patterns and a comparison of PGRs of four test meals in a visual and individualized manner. Dietary advice about healthy food choices will be given as is the routine recommendation in China Medical Nutrition Therapy Guideline for Diabetes (36): (1) an appropriate amount of fish, eggs, low-fat milk, lean meat, and reduction in fatty meat in the diet, (2) more fiber-rich food, such as whole grains, vegetables, and fruits, (3) avoidance of simple sugars and refined carbohydrates, and (4) appropriate energy intake. Each participant's current status of body weight, physical activity, and dietary behaviors collected at the baseline survey will be considered in providing dietary advice.

A dietary approach of pre-load (P + L) or mid-meal snack (S + L) with lower iAUC from test results will be recommended to follow during the next 4 weeks. Considering rush time in the morning before breakfast, pre-load or snacks will be suggested to consume before lunch and dinner. For participants who are suggested to follow S + L, three Fitmeal at each morning tea and afternoon tea are asked to consume, approximately at 10 a.m. and 4 p.m., 2 h before lunch and dinner. If suggested to follow P + L, participants are asked to consume three Fitmeal 30 min before lunch and dinner, ~11:30 a.m. and 5:30 p.m. Blood glucose meter and testing supplies will be provided to participants for self-monitoring of blood glucose (SMBG) with six times a day in a manner of paired pre-meal and 1 h-post-meal, at least 2 days per week.

From week 6, participants will be invited to the research site to complete an end-point questionnaire and physical examination, another CGM will be applied to monitor glucose profile for at least 72 h, and a food diary and the time to start each meal are required to record using the log book for 2 continuous days (midnight to midnight) from the second day of applying CGM. At the end of this trial, the comprehensive glucose profiles and the impact of diet on glucose levels will be reviewed and discussed with each participant in face-to-face counseling for facilitating their understanding and compliance with the dietary strategy to stabilize glucose levels. The study flow chart can be seen in Figure 2.

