**Physical measures**										
Weight and BMI	X							X	X	X
Height	X									
Waist circumference	X									X
Body fat %	X									

Glycemic metrics will be calculated with values from CGM and SMBG. Participants who have signed the consent form will wear the CGM (FreeStyle Libre 1, FSL1, Abbott Diabetes Care, Inc., Alameda, CA) two times, monitoring for 7 days on week 1 and 3 days on week 6, respectively. The FSL1 is the most used biosensor for intermittent scanned CGM. All glucose data will be given each 15 min with a total of 96 readings every 24 h. From all these glucose measurements, several glucose metrics are calculated and reported on a 24-h basis average, including the percentage of time in a range from 3.9 to 10 mmol/L (TIR), percentage of time above range (TAR), percentage of time below range (TBR), a standard difference of mean glucose (SD), mean amplitude of glycemic excursions (MAGE), %CV, average glucose concentration (AG), incremental areas under the curve (iAUC), and post-prandial glycemic excursions (PE). Changes in glycemic metrics are calculated by subtracting the averaged values obtained on day 1 and 2 with CGM use at the baseline from the averaged values obtained on the second and third days of CGM use at the end-point. iAUCs will be calculated to represent the PGRs of four test meals from day 3 to 6, respectively. SMBG will be tested by glucose meter data (Qin Zhi, Sinocare, Inc., Changsha, China) six times a day in a paired test regimen at pre-meal and 1 h post-meal, at least 2 days per week from week 2 to week 5. SMBG frequency, average fasting, and pre-meal blood glucose concentrations, average 1 h post-prandial glucose concentrations (1hPG), and 1 h post-prandial excursions (1hPE) will be calculated. CGM and glucose meter data (An Wen/Qin Zhi, Sinocare, Inc. Changsha, China) will be uploaded automatically to the data platform and will be analyzed at the end of each monitoring period.

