### Outcome

#### Primary outcome

The 3-h post-lunch incremental areas under the curve of post-prandial glycemic responses (iAUC) using CGM are compared between the low-GI biscuits as pre-load food (P + L) or mid-meal snack (S + L) and their isocaloric standard control of co-ingestion (CL) and placebo control (W + L) in women with recent GDM. Primary outcomes also include differences in CGM measures (AG, SD, %CV, MAGE, TIR, TAR, TBR, and PE) and GA after a 4-week intervention compared with those variables at the baseline.

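### The paired t-test named for the phase-2 before–after outcomes uses only women with a week-6 value, so it gives a completers-only estimate for an objective worded for all participants

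*Protocol article*

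**What the plan says.** The Introduction gives the aim of the second phase as to "observe before–after differences among all participants in their glycemic control", measured by CGM metrics and glycated albumin, and to compare those differences between the two dietary strategies. The text after Figure 1 says that the 4-week intervention "based on within-subject meal test results will be followed for all participants to compare changes in PGRs from the baseline".

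The Primary outcome section adds to the phase-1 iAUC the changes in AG, SD, %CV, MAGE, TIR, TAR, TBR, PE and GA "after a 4-week intervention compared with those variables at the baseline". That makes nine phase-2 outcomes with primary status.

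The data-collection text after Table 3 defines the change: "Changes in glycemic metrics are calculated by subtracting the averaged values obtained on day 1 and 2 with CGM use at the baseline" from the averages of the second and third CGM days at the end-point. Both visits are therefore needed. The Statistical analysis section gives one method: "Comparison between baseline and end-points is assessed by paired" Student's t-test.

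Dropout is mentioned once, under Sample size: "Anticipating a 20% dropout rate, 49 subjects should be enrolled to obtain a final sample size of 39". Enrolment is then rounded up to 52, 13 per centre.

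**The concern.** A woman who leaves after the test week, or who misses the week-6 CGM and blood draw, has no change score and drops out of every phase-2 comparison. Her baseline CGM and GA are already held by then. The paired mean describes everyone who started only if loss is unrelated both to baseline glycemia and to response.

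There are two distinct ways this can fail. If loss depends on baseline, completers start from an unrepresentative level, and regression to the mean produces a change that is not real. If women leave because the approach is not helping, the completer mean overstates the benefit. Phase 2 has no control arm in which similar losses might offset either effect.

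The protocol's own rationale makes unrelated dropout hard to take for granted. It argues that women comply when they see that a diet works for them, and each woman is shown her own meal-test results before the 4 weeks begin.

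**Working it through.** **1. The plan's own figures.** With SD 32.9 and difference 20 mmol·min/L, 90% power, two-sided α = 0.05/k, and the SD read as that of the within-woman difference:

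n = (32.9 × (z₁₋α/₂ + z₀.₉₀) / 20)²

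The number of comparisons k is not stated. The normal formula gives 37 for k = 3 and 39 for k = 4. The t-based n for k = 3 is 40, and power at n = 39 is then 89.6%. The stated 39 is reproduced within tolerance. Inflation: 39 / (1 − 0.20) = 48.75, so 49. These figures are sound and the point below does not touch them.

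**2. How many women could be lost.** 52 × 0.20 = 10.4, leaving 41.6, so about 42 pairs. This takes the whole allowance as lost before week 6. The article does not divide it between phases, so this is an upper reading.

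**3. Dropout related to baseline.** Assumptions, none given in the documents: outcome in SD units, no true change, 20% dropout by a logistic model on baseline with odds ratio (OR) per SD above 1, so that women with high values leave more often, and baseline–end-point correlation ρ. If completers' mean baseline lies m SD below that of all women, the expected spurious change is

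bias = (1 − ρ) × m

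Numerical integration at 20% dropout gives m = 0.079, 0.129 and 0.186 for OR 1.5, 2 and 3. Example: OR 2, ρ = 0.5 gives 0.5 × 0.129 = 0.064. A simulation (52 women, 8,000 runs per setting) agrees up to simulation error. Each cell shows bias in SD and, in brackets, the rejection rate at nominal 5%:

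| OR per SD | ρ = 0.3 | ρ = 0.5 | ρ = 0.7 |
|---|---|---|---|
| 1.5 | 0.056 (6.2%) | 0.036 (5.6%) | 0.024 (5.2%) |
| 2 | 0.091 (7.8%) | 0.061 (6.6%) | 0.036 (5.6%) |
| 3 | 0.129 (10.7%) | 0.096 (9.2%) | 0.056 (7.5%) |

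This is about 0.2 to 0.7 of the standard error. The sign here is a spurious rise, because high-baseline women are lost. Loss of low-baseline women gives a spurious fall.

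The likelihood estimate that uses all baselines has absolute bias of at most 0.003 and essentially the same spread (0.154 against 0.153 at OR 2, ρ = 0.5).

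**4. Dropout related to response.** Let dropouts' mean change be a fraction f of completers' (an assumption). With 20% loss, the all-participant mean is (0.8 + 0.2f) times the completer mean:

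- f = 0: 0.80, so completers overstate by 1/0.80 − 1 = 25%
- f = 0.5: 0.90, overstatement 11%
- f = 1: 1.00, none

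If only 10% were lost in phase 2 and f = 0, the overstatement is 1/0.90 − 1 = 11%.

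For scale, take a completer effect of 0.5 SD of change. The all-participant effect is 0.8 × 0.5 = 0.40, the bias is 0.10, and 0.10 × √42 = 0.65 SE. If this dropout is unrelated to baseline, the mixed model also returns about 0.50, so it does not repair this case.

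**The case against.** **Silence on missing data.** The article neither excludes nor retains women without week-6 data, and analysis sets and imputation rules commonly sit in a fuller document that is not shown. This stands: the absence of such a rule is not a fault. The point concerns the method that is named, which on observed data is a complete-pairs analysis.

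**The wording about all participants.** In the Introduction it stands beside a comparison between the two strategies, so it may mean pooled across strategies. A reader might infer a firm commitment to analyse women without follow-up. The text does not go that far, but neither does it describe completers only.

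**The 20%.** A reader might also infer that a fifth of the women are expected to be missing at week 6. The documents do not support that: the figure belongs to the iAUC sample size, and some loss may occur in week 1.

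**Size and direction.** The odds ratios and correlations are assumptions. The middle setting gives 0.06 SD and 6.6% rejection, and 11% needs the extreme corner. Where lower values are better, loss of high-baseline women looks like worsening and works against a claim of benefit. All of this stands.

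**The remedy.** A mixed model does not deal with response-driven dropout, which is why a sensitivity analysis must accompany it. Assessment of women who stop the biscuits needs no new rule: "From week 6, participants will be invited to the research site to complete an end-point questionnaire and physical examination", with no restriction to those still taking them.

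**Disclosed limits.** The Discussion admits that phase 2 is unrandomised and unblinded. It does not mention attrition.

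**Conclusion.** The concern holds in limited form. The named test gives a completers-only estimate for outcomes with primary status whose objective is worded more widely, and a better method is available at almost no cost.

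The bias is nil if dropout is unrelated to baseline and response. With baseline-related dropout, the assumed ranges give 0.02 to 0.13 SD and a false-positive rate of about 5% to 11% per outcome, in a direction set by who leaves. With response-related dropout, the completer mean is 25% too large if all 20% are lost in phase 2 and had no change, and less otherwise. The documents do not show that bias will occur, and the sample size is unaffected.

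**What to change.** In the Statistical analysis section, replace the paired t-test for phase-2 outcomes with a two-visit repeated-measures mixed model: visit as fixed effect, unstructured covariance, REML. Include every woman with a baseline value and report the week-6 minus baseline contrast. This removes bias from baseline-related dropout with essentially no loss of precision.

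Add one sensitivity analysis that assigns zero change to women without a week-6 value, to cover dropout driven by response.

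If the paired t-test is kept, state that the phase-2 result applies to completers.

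The cost is a change of wording, with no added participants, visits or measurements. The analysis becomes slightly less simple, and the sensitivity analysis may show a smaller effect.
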